## Dissemination

The Trial Steering Committee will provide overall trial supervision. The main ethical consideration is to ensure that the risk of harm to participants is minimised and that they are fully informed of any risks. Lipid lowering agents are not permitted during the trial. Should an individual's LDL-cholesterol rise above >5 mmol/L, this will be recorded as an adverse event and they will be withdrawn from the study, with general practitioner referral for appropriate medication.

The research dietitian, at study visits, will monitor the condition of the participants during the trial, requesting evaluation of potential harms by the participants’ HIV physician during routine clinic visits. All adverse events, whether considered trial-related or not, will be documented in the participant's case report form, and reported to the Trial Steering Committee and Sponsor.

Participants will be free to withdraw from the study at any time. If participants withdraw from the intervention, they will be asked if they would allow data to be collected at routine clinic appointments.

Electronic trial data will be entered into the encrypted and password protected trial computer, stored on the secure hospital server and archived for 5 years after study completion. Paper copies will be held in the research office for purposes of potential data checking, and shredded 1 year after study completion.

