**Methods and analysis:**

60 adults with stable HIV infection on antiretroviral treatment and low-density lipoprotein cholesterol >3 mmol/L will be recruited from 3 West Midlands HIV services. Participants will be randomised 1:1 to 1 of 2 dietary interventions, with stratification by gender and smoking status. Participants allocated to Diet1 will receive advice to reduce saturated fat intake, and those to Diet2 on how to adopt the Mediterranean Portfolio Diet with additional cholesterol-lowering foods (nuts, stanols, soya, oats, pulses). Measurements of fasting blood lipids, body composition and arterial stiffness will be conducted at baseline, and month 6 and 12 of the intervention. Food intake will be assessed using the Mediterranean Diet Score, 3-day food diaries and metabolomic biomarkers. Questionnaires will be used to assess quality of life and process evaluation. Qualitative interviews will explore barriers and facilitators to making dietary changes, and participant views on the intervention. Qualitative data will be analysed using the Framework Method. Feasibility will be assessed in terms of trial recruitment, retention, compliance to study visits and the intervention. SD of outcomes will inform the power calculation of the definitive RCT.

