### Recruitment

Recruitment will be conducted using a number of methods: advertising poster in waiting room for patients; referral from multidisciplinary team providing HIV care; and screening of patient blood results for LDL-cholesterol >3 mmol/L. Patients will be assessed for eligibility by the researcher. Eligible patients will be handed or posted an invitation letter and participant information sheet containing details of all the interventions and assessments to be expected. To avoid contamination, the description of the dietary interventions will be general and applicable to both groups. Patients will be given at least 24 h to consider the information before being contacted to confirm the date of their next routine blood test appointment, and reminded to attend in a fasted state, with no food consumed 12 h prior to the appointment time. Written informed consent will be obtained from all participants at their first trial visit, prior to baseline measurements.

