### Intervention design

All participants, in both groups, will be invited to attend three individual consultations with the research dietitian, and will receive further telephone reinforcement and support during the 6-month intervention period. Appointment times will be offered between 08:00 and 19:00, enabling flexibility for participants who are working. This will be followed by a 6-month maintenance period, with routine clinic visits only. The same research dietitian, experienced in HIV nutritional care, will provide all consultations.

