### Outcome measures

The primary outcomes for this study are feasibility and acceptability of trial procedures for recruitment, retention, data completion and the intervention. The protocol will be considered viable for a definitive RCT without modification if the following outcomes are met:
Recruitment rates of at least 50% of eligible patients;Attrition rate of <20% by 6 months;Compliance rate of 60% to trial.

If these outcomes are not met, the protocol will be modified in light of the study's findings.

Recruitment rate will be measured as proportion of eligible patients who are subsequently enrolled. Methods of recruitment will be compared: difference between recruitment rate from systematic methods (screening results) and ad hoc methods (posters, referral by multidisciplinary team). Reasons will be sought for declined participation. Appropriateness of eligibility criteria and their practical application for definitive trial will be explored.

Attrition rate is defined as both discontinuation and loss to follow-up of participants at 6 months. Logistic regression will be conducted to assess whether completion is associated with age, gender or allocation preference. Reasons for discontinuation will be sought from participants. The target of 20% (with precision of 10%) is based on the mean attrition rate from five Portfolio Diet studies (13%) and systematic review evidence (18%),^20^ although attrition has ranged from 25%^24^ to 42%^73^ in other HIV diet studies. Acceptability of the intervention and group allocation will be explored by questionnaire, and assessed by comparing attrition rates between the two groups.

Attendance to appointments, collection of supplied foods and completion of food diaries will be used as indicators of participation and study compliance.

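### The rule for LDL above 5 mmol/L ends study follow-up as well as the diet, so a few month-12 measurements are lost for a reason tied to the target outcome

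*Protocol article*

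**What the plan says.** All references are to the protocol article.

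- **Dissemination, the rule.** When LDL-cholesterol rises above 5 mmol/L, "this will be recorded as an adverse event and they will be withdrawn from the study", and the general practitioner is asked to consider medication. The same paragraph states: "Lipid lowering agents are not permitted during the trial".
- **Dissemination, later data.** "If participants withdraw from the intervention, they will be asked if they would allow data to be collected at routine clinic appointments". This covers withdrawal from the intervention. Nothing extends it to people withdrawn from the study under the LDL rule.
- **Abstract, Methods and analysis.** "Measurements of fasting blood lipids, body composition and arterial stiffness will be conducted at baseline, and month 6 and 12 of the intervention".
- **Intervention design.** After the 6-month intervention, "This will be followed by a 6-month maintenance period, with routine clinic visits only".
- **Outcome measures.** "Attrition rate is defined as both discontinuation and loss to follow-up of participants at 6 months", with a target below 20%. Attrition is also compared between arms as a measure of acceptability. Completeness of data is among the primary feasibility outcomes.
- **Statistical analysis plan.** Participants are analysed as allocated, by ANCOVA on baseline. The SD of each outcome is to inform the definitive trial. The only LDL contrast given a size and a time is about 0.5 mmol/L at 6 months.

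**The concern.** LDL is the outcome that the diets are meant to change, and here its own value decides who leaves follow-up. Exits are likely to be more frequent in the arm with the smaller LDL reduction, so the missing data depend on outcome and probably on arm.

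The safety actions are the adverse-event record and the referral. Neither needs the participant to miss later measurements, provided the bar on lipid-lowering drugs is lifted once the rule has been triggered. The loss covers month-12 body composition, arterial stiffness and questionnaires as well as LDL. The pilot is also meant to supply the framework for a definitive trial, which would inherit the rule if nothing is changed.

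**Working it through.** **1. When the rule can act.** After baseline, the scheduled lipid measurements are at month 6 and month 12. On that schedule the first possible trigger is the month-6 sample. That value has then been observed, and the 6-month intervention is over. What is lost is month 12.

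**2. The plan's own figure.** The rule carries no figure. The only related one is the attrition interval: 0.20 ± 1.96 × √(0.20 × 0.80 / 60) = 0.20 ± 0.101, or 9.9% to 30.1%. This reproduces the stated 10% to 30%.

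**3. Inputs for the size of the loss.**
- From the article: threshold 5, entry LDL above 3, 60 participants randomised 1:1 (30 per arm), between-arm difference 0.5 mmol/L.
- Assumed, because the article gives no LDL mean or SD: mean entry LDL 3.7 or 4.2; true LDL SD 0.8; within-person SD 0.35; true changes −0.15 (Diet1) and −0.65 (Diet2), with individual SD 0.3.
- The rule is applied if baseline is at most 5 and the month-6 value is above 5, since the text speaks of a rise.

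**4. Simulated results, trigger at month 6.**

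| | Mean entry 3.7 | Mean entry 4.2 |
|---|---|---|
| Exits, Diet1 | 1.23% | 4.60% |
| Exits, Diet2 | 0.16% | 0.79% |
| Expected exits of 60 | 30 × (0.0123 + 0.0016) = 0.42 | 30 × (0.0460 + 0.0079) = 1.62 |
| Chance of at least one exit | 1 − 0.9877³⁰ × 0.9984³⁰ = 0.34 | 1 − 0.9540³⁰ × 0.9921³⁰ = 0.81 |
| Month-12 difference, full data | −0.500 | −0.500 |
| Month-12 difference, complete cases | −0.493 | −0.479 |
| Imputed from arm, baseline and month-6 LDL | −0.500 | −0.500 |
| Within-arm SD, full to complete-case | 0.715 to 0.707 | 0.821 to 0.813 |

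With a residual SD of 0.56, the standard error is 0.56 × √(4/60) = 0.145. The shifts of 0.007 and 0.021 are about 5% and 14% of it. The SD falls by 1.0% to 1.2%.

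**5. Sensitivity.** With true and within-person SDs of 0.6/0.25, 0.8/0.25 and 0.8/0.45, expected exits are 0.22 to 0.53 of 60 at mean 3.7 and 1.18 to 2.10 at mean 4.2. A harsher setting assumes no LDL fall in Diet1, mean 4.0 and SD 0.9 before the entry cut, within-person correlation 0.6, and entry limited to LDL of 5 or below. It gives 10.2% against 2.8%, or 30 × (0.102 + 0.028) = 3.9 of 60, and a complete-case difference of −0.466.

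**6. Attrition, conditional case only.** Suppose the exits in step 4 also count towards 6-month attrition. Staying below 20% means at most 11 of 60 lost. With other attrition p and exit proportion q, the total is p + (1 − p)q, with q = 0.42/60 or 1.62/60. Outcome measures cites 13% and 18% as earlier attrition rates.

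| Other attrition | P(at most 11 lost), no LDL exits | With LDL exits |
|---|---|---|
| 13% | 0.917 | 0.892 or 0.798 |
| 18% | 0.606 | 0.561 or 0.433 |

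If everyone had one routine lipid test before month 6, 0.41 or 1.62 of 60 would leave before month 6. The month-6 complete-case difference would then be −0.492 or −0.479.

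**7. What medication does to month-12 LDL.** If exits stay in follow-up and all are treated, the as-observed month-12 difference is −0.489 (mean 3.7) or −0.462 (mean 4.2) for an assumed drug effect of 1.0 mmol/L, and −0.484 or −0.443 for 1.5. Above a drug effect of about 0.6 to 0.7, the as-observed contrast lies further from −0.500 than the complete-case one.

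**The case against.** **The harm is negligible and LDL is exploratory.** This largely stands for LDL. The primary outcomes are feasibility and acceptability, and the month-12 LDL difference can be recovered from the month-6 value. It does not answer the loss of body composition, arterial stiffness and questionnaire data.

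**Simply continuing follow-up could make the LDL contrast worse.** This stands, as step 7 shows, and the fix must therefore say how on-medication values are handled.

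**Withdrawal has a safety purpose.** This stands in part. With lipid-lowering drugs barred during the trial, leaving the study is what frees the participant to take them. Ending follow-up is unnecessary only if the bar is lifted as well.

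**The routine-appointment offer may already cover these people, or the full protocol may.** A generous reading is possible, and routine blood tests do exist (Recruitment: "confirm the date of their next routine blood test appointment"). The wording is nevertheless limited to withdrawal from the intervention, and the article does not say that routine appointments include body composition or arterial stiffness. The objection is to a rule that the article states, so it does not depend on missing detail.

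**Attrition should include these exits, because a definitive trial would suffer them too.** This is a fair view. "Reasons for discontinuation will be sought from participants", and adverse events are documented, so such exits could be identified. The definition does not say whether a month-6 trigger counts.

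**Stronger readings that a reader might infer.** One is that the rule contradicts the intention-to-treat plan. It does not: analysis as allocated remains possible, with fewer month-12 data. Another is that it biases the 6-month LDL comparison, but on the stated schedule the month-6 value is observed before the rule acts. A third is that it may remove about 15% of Diet1. Such a figure arises only if people who entered above 5 are also removed, whereas the text speaks of LDL rising above that level.

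**Conclusion.** The point holds as a cheap improvement. As written, the rule ends study follow-up because of the target outcome's own value, and no other part of the article repairs this. On the stated schedule, and under the main assumed LDL distributions with their SD variations, about 0.2 to 2 of 60 participants lose month 12, mostly in Diet1. The harsher setting gives about 4.

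The month-6 LDL contrast is unaffected. The month-12 LDL bias is negligible to small and can be removed using month-6 LDL. The data that cannot be recovered are the other month-12 measures in those few people. Any effect on the attrition criterion is conditional: it needs a routine test before month 6 to trigger the rule, or a month-6 trigger to be classed as discontinuation, and the article settles neither. The size of every effect rests on assumed LDL values.

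**What to change.** Amend the Dissemination paragraph as follows.

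- Keep the adverse-event record and the GP referral.
- In place of withdrawal from the study, stop the diet if needed, permit lipid-lowering drugs after the trigger, and invite the participant to the remaining planned visits in the allocated arm.
- Retain the triggering LDL value and record the date medication starts.
- For the diet effect on LDL, treat month-12 values measured on medication as missing and impute them from arm, baseline and month-6 LDL. Report the as-observed (treatment-policy) result alongside.
- Use body composition, arterial stiffness and questionnaire data as observed.
- Report LDL-triggered exits on a separate line beside the attrition rate and its between-arm comparison.

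**Cost.** The measurements are already planned, so no new procedure is needed. The change does alter a safety rule and needs ethics approval. A few on-medication values must be flagged, and one extra analysis is required.

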## Discussion

This study is timely for several reasons. First, CVD remains the largest cause of mortality in the UK^77^ and will continue to rise in the ageing HIV population. Second, current guidelines recommend dietary intervention as first-line treatment for HIV dyslipidaemia.^13–15^ These recommendations are based on guidelines for the general population^16^
^17^ where dietary advice, with emphasis on reduction of saturated fat, has been shown to reduce CVD risk and mortality.^18^ Presuming that the reduction in CVD achieved by dietary intervention in the general population will be mirrored in the HIV population is problematic, given the complexity of CVD among the HIV population and the potential of different contributing mechanisms.^19^ Third, there are no studies on dietary intervention, of any kind, in the HIV population in the UK. Also, there are no known studies on cholesterol-lowering foods, nor on the Portfolio Diet, in the HIV population internationally. Components of this diet have been incorporated into the UCLP (HEART UK), but have yet to be evaluated in the UK population. Therefore, findings from this feasibility study utilising the Mediterranean Portfolio Diet in the HIV population could potentially inform the acceptability of this diet in the wider population.

As indicated by the lack of effect found with diets low in saturated fat, further studies with interventions of greater intensity and sufficient duration are required to elucidate the full potential of dietary intervention, and to ascertain whether modifying the known marker of increased risk (LDL-cholesterol) modifies the risk itself (CVD). Therefore, this study aims to examine whether a diet low in saturated fat, which also incorporates functional foods and a Mediterranean style, reduces blood lipid levels in patients with HIV infection. If this dietary intervention can significantly reduce blood lipid levels, patients may have the option of reducing their CV risk without the need for lipid-lowering medications (with attendant increasing pill and side effects) or switching antiretroviral drugs (with the potential risk of losing virological control of HIV). A reduction of 1 mmol/L in LDL-cholesterol reduces the risk of dying from heart disease by nearly 20% in the general population,^78^ but this has not been ascertained in the HIV population.

Piloting this trial format will be important in determining any feasibility challenges and will be used to estimate the time, resources and sample size required for a full-scale RCT to answer these questions.
